## Abstract

**Background:**

Novel interactive and pictorial health education tool named Diabetes Conversation Map (DCM) might be effective for the improvement of diabetes management self-efficacy (DMSE) and diabetes distress (DD) among diabetic patients in lower middle-income setting. This study protocol will assess the effectiveness of DCM as compared to routine care (RC) to improve DMSE, decrease DD and glycated hemoglobin (HbA1c) among patients with type 2 diabetes (T2DM).

**Methods:**

This will be two arms randomized controlled trial, conducted at national institute of diabetes and endocrinology (NIDE) in Karachi, Pakistan. A sample of 120 T2DM patients of age 30–60 years with suboptimal diabetes control will be screened through eligibility criteria and DD screening tool. Patients who fulfill the eligibility criteria and have diabetes distress will be randomized into interventional and control arm. The intervention arm will receive four education sessions (40 min each) using DCM for 4 weeks duration of enrollment. Controlled arm will receive RC. DMSE and DD will be measured using the validated Likert tools at baseline and after 3 months of enrollment. Latest results of HbA1c will be retrieved from the respective medical record files at baseline and 3 months. Change in DMSE, DD scores and HbA1c levels within groups (pre-post) and between the groups after 3 months of enrollment will be compared. Multivariable linear regression will be conducted to adjust for any potential confounders.

**Discussion:**

In a study in UK, 70% of the patients with diabetes reported DCM had helped them in controlling their diabetes and recommended this method to teach other patients with diabetes also. In China, a study found that patients with diabetes who received DCM based education had significantly lower DD and significantly higher diabetes empowerment score after six months of the intervention as compared to the traditional counselling. A cross sectional study conducted in Pakistan also demonstrated that teaching based on DCM was useful in improving the knowledge, attitude and practices of patients with T2DM. Besides, no other study has evaluated the effectiveness of these novel tools for DMSE and diabetes distress DD in well-designed, sufficiently powered clinical trials.

**Trial registration:**

ClinicalTrials.gov Identifier: NCT03747471. Date of registration: Nov 20. 2018. Version and Date of Protocol: Version 1, IRB Approval date 28 June 2018.

**Electronic supplementary material:**

The online version of this article (10.1186/s12889-019-7266-3) contains supplementary material, which is available to authorized users.

## Background

During the last three decades, the age standardized prevalence of T2DMT2DM has doubled from 4.7% in 1980 to 8.5% in 2014 [1].

The prevalence adjusted for the world by International Diabetes Federation (IDF) is 24% in Saudi Arabia, 23% in Kuwait and Qatar each, 7.8% in Australia, 9.2% in USA, 5% in UK, 9.1% in India, 6.3% in Bangladesh, 9.9% in Iran, 8.3% in Afghanistan, 9% in China, and 7.9% in Pakistan [2].

Uncontrolled diabetes can cause serious acute complications associated with either abnormally high blood glucose resulting in diabetic ketoacidosis (DKA) and hyperosmolar coma or abnormally low blood glucose level resulting in seizures and unconsciousness. Poorly controlled diabetes in the long run causes serious damage to the heart, kidneys, blood vessels, nerves and eyes [3]. According to an estimate, 1.5 million deaths were caused by diabetes in 2012. The percentage of deaths attributable to high blood glucose or diabetes that occurs prior to age 70 is higher in low- and middle-income countries than in high-income countries [2].

As diabetes mellitus affect all aspects of life, its care plan is interlinked with daily actions of the diseased person and hence the diabetic patients also play an important role in the control and management of their disease [4]. DMSE is considered as an important pre-requisite for the success of diabetic control and self-management [5]. Also, it is considered as an independent part of basic skills. Self-Efficacy (SE) is a social cognitive theory proposed by Albert Bandura in 1977. According to Bandura, self-efficacy is a belief in one’s ability to influence events that affects one’s life and control over the way these events are experienced [6]. It further argues that individuals will act when they believe they are able to do it and will avoid any action which they believe they may not be able to perform. Furthermore, the theory proposes that self-efficacy plays an important role in predicting the individuals’ behavior. A study conducted among diabetic patients in Iran, reported strong positive correlation between self-efficacy and diabetes self-care management [7].

On the other hand, the stress associated with diabetes management, its complications or risk of developing complications and living with diabetes itself has the potential of causing significant emotional distress among patients with diabetes. In 1995, the concept of DD was put forward by Polonsky and his team to highlight the negative emotional impact of living with diabetes [8]. Studies from the developed world such as Europe, USA and Australia have shown that about a quarter of the diabetic adult population are experiencing DD [9–11]. Similarly, research among patients with diabetes has shown association between reduction in DD and significant improvement in blood glucose levels [12, 13].

Traditionally, patients with diabetes used to receive education related to their disease process, metabolic control, exercise and diabetic diet through didactic lectures, brochures, pamphlets, and face to face counseling [14]. Among novel methods, Diabetes Conversation Maps (DCM) are considered as useful tools for the educational empowerment of diabetic patients [15]. These are interactive pictorial tools designed in such a way that it does not need formal education for common understanding. In developing countries like Pakistan, where the literacy rate is very less, these tools might prove to be effective for the control of diabetes and its associated complications [16]. DCM have been used and tested in several countries predominantly in the developed world. In the developing region, while it has shown some impact during the observational studies, literature generated from randomized control trials is still limited. Patients in the developing region has different level of education and environmental exposures such as access to internet and social media, they have different socio-demographic characteristics and hence might behave differently from their counterparts in the developed world. Therefore, there is a need of well-designed randomized controlled trial to evaluate the effectiveness of DCM versus routine diabetic care (RC) in DMSE and DD in a low middle income setting of Karachi, Pakistan.

## Methods/design

### Aim of the study

The aim of this study protocol is to assess the effectiveness of DCM as an educational tool in comparison to routine diabetic counseling for improving the DMSE and DD among patients with T2DM.

### Study design and randomization

This will be two parallel arms randomized controlled trial conducted in a public sector tertiary care hospital of Karachi, Pakistan. The randomization will be performed through the generation of random digit numbers from 1 to 120 using Microsoft excel 10 (*RANDBETWEEN* function). Numbers such as 60 or below will be assigned to diabetes conversation map (acronym DCM; *n* = 60) and numbers above 60 will be assigned to routine counseling (acronym RC; n = 60). Random numbers and their corresponding assignment will be sealed in the envelops, kept in sequence and open consecutively as patients are screened and found eligible for enrollment into the study. Principal Investigator ([name]) of this project will open the envelopes for each participant to allocate the intervention.

### Study setting

This study will be conducted at National Institute of Diabetic and Endocrinology (NIDE) Ojha campus, located at Dow University of Health Sciences (DUHS). This is a public sector specialized teaching hospital with both inpatient and outpatient facilities. Average daily turnover of diabetic patients in the outpatient department is about more than 200. For those who require hospitalization, 250 bedded inpatient facilities are available. All the patients are assigned a unique medical record number and both laboratory, and essential medical records are electronically archived using this unique number. A subsidized fee for consultation and laboratory investigation is charged from affording patients. Welfare funds are used to pay the treatment cost of those who cannot afford to pay themselves.

### Study duration

This study will be completed in 6 months duration starting from November 25, 2018.

### Study population

#### Inclusion criteria

Patients aged 30–60 years, visiting the diabetes clinics of NIDE, diagnosed with T2DM for at least 5 years, HbA1c levels of > 7%, and found to be positive for diabetes distress (DD) based on validated DD screening tool (section 3 of Additional file 1) will be included in the study.

#### Exclusion criteria

Patients with T2DM with major disabilities, diagnosed with mental health problems/ cognitive pattern not intact, with major diabetes related complications, and living outside Karachi will be excluded from the study.

### Operational definitions

Diabetes control: Patients with T2DM with glycated hemoglobin (HbA1c) ≤7 will be considered as diabetes control.

Suboptimal control of diabetes: Patients with T2DM with HbA1c more than 7% at the time of enrollment will be considered suboptimal control of diabetes.

### Sample size

A study from China [17] reported mean DD score of control and intervention group at baseline as 32.77 ± 14.57 and 26.08 ± 9.92 respectively (*p* value 0.073). After six months of the intervention the respective scores were 30.09 ± 12.14 and 22.79 ± 4.95 (p value 0.014). Aiming for a higher average difference of the differences (difference of 7.30) as compared to the study from china (0.62) between the intervention and control arm (which is also clinically significant), considering 95% confidence interval and 80% power of the test to detect the given difference, the minimum sample size to achieve the objective of this study will be 88 (44 in each group). After adding attrition rate, a total of 120 subjects i.e. 60 in RC arm and 60 in DCM arm will be enrolled in this study.

### Enrollment and data collection procedure

The principle investigator (PI) will take permission from related authority. The PI will be sitting in the waiting area outside the clinic where the physician will refer all the patients diagnosed with T2DM with suboptimal management. After screening based on eligibility criteria, informed consent will be taken, and participant will be randomized. Structured Questionnaire translated in Urdu language and back translated in English will be used for collecting demographic, clinical, and laboratory data. After 3 months of enrollment, a follow up interview will be conducted using the same questionnaire and blood test for HbA1c to see the change in baseline measurements across the two groups.

#### Dependent variables

Diabetes Management Self-Efficacy (DMSE) and Diabetes Distress (DD) and HbA1c are dependent variable in this study.

#### Independent variables

This will include age, gender, BMI, education level, occupation, marital status, time since diabetes diagnosis, time since diabetes treatment, type of treatment for Diabetes e.g. Tablets, insulin etc. use of smart phones, use of internet, monthly income and intervention (DCM or RC).

#### Measurements of DMSE and DD

The DMSE will be measured using validated DMSE scale (See Section 2 of Additional file 1) [18]. The scale has 20 items comprised of 4 domains; 1) nutrition specific and weight, 2) medical treatment, 3) physical exercise, 4) blood sugar. Each item is scored on 11-point Likert scale (0 = completely unable to 10 = completely able). Possible score ranges from 0 to 200, with higher score representing higher DMSE. The assessment of DMSE will be measured by taking mean scores and then compared at pre and post intervention.DD will be screened using validated DD scale (See Section 3 of Additional file 1) [19]. The scale has two parts; part 1 is consisting of two items asking about feelings of overburden due to demands of living with diabetes and feelings of failure with diabetes routine; the aim of part 1 is to screen for the presence of DD. Part 1 will be administered before the enrollment of the patient to screen for the presence of DD. If DD is present, part 2 will begin consisting of 17 items to score the extent of DD. Each item is scored on a Likert scale ranging from 1 (not a problem) to 6 (a very serious problem). According to the instructions of DD scoring sheet, total DD will be measured with mean score while dividing the sum of all items by 17. Similarly, mean scores of emotional burden (items 1, 3, 8, 11, 14), physician-related distress (items 2, 4, 9, 15), regimen-related distress (items 5, 6, 10, 12, 16) and interpersonal distress (items 7, 13, 17) will be measured by dividing the sums of respective items by respective numbers of items. The mean score of ≥3 will be the threshold for being distressed.

#### Measurement of HbA1c

Diabetic patients visiting NIDE are routinely advised for HbA1c to assess their diabetes control. These tests are performed at subsidized cost at the clinical laboratory of DUHS using the standardized methods. We will access the results of latest HbA1c tests at the time of screening and then 3 months after the enrollment into the study. HbA1c values will be categorized into two groups; 1) subjects where HbA1c < = 7 will be considered as patients with good diabetic control and 2) subjects where HbA1c > 7 will be considered as patients with sub-optimal diabetic control, therefore eligible for inclusion in the study.

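### The 3-month HbA1c is the latest routine record result in two sections and a follow-up blood test in a third, and the record rule can admit a value drawn before or during the sessions

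*Protocol article*

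**What the plan says.** Three places in the protocol article say where the HbA1c values come from.

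- **Abstract, Methods:** "Latest results of HbA1c will be retrieved from the respective medical record files at baseline and 3 months".
- **Measurement of HbA1c:** "Diabetic patients visiting NIDE are routinely advised for HbA1c to assess their diabetes control"; the section adds that the university's clinical laboratory runs these tests at a subsidised price, and then states "We will access the results of latest HbA1c tests at the time of screening and then 3 months after the enrollment into the study".
- **Enrollment and data collection procedure:** three months after enrolment, "a follow up interview will be conducted using the same questionnaire and blood test for HbA1c to see the change in baseline measurements".

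HbA1c has two roles. It is an outcome: "Diabetes Management Self-Efficacy (DMSE) and Diabetes Distress (DD) and HbA1c are dependent variable in this study". It also decides eligibility: Inclusion criteria requires "HbA1c levels of > 7" per cent, and Operational definitions ties the same threshold to a point in time: "Patients with T2DM with HbA1c more than 7% at the time of enrollment will be considered suboptimal control of diabetes".

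Plan of analysis tests HbA1c before and after within each arm (paired t test) and between arms after the intervention (independent t test). The Abstract also speaks of comparing change between the groups. A sensitivity analysis is promised for the effect of missing data.

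**The concern.** The first two places describe looking up a result that already exists. The third describes a test done at follow-up. These are different rules for the same endpoint, and no sentence connects them.

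The lookup rule has a particular weakness: *latest* fixes the moment at which the record is read, not the moment at which blood was drawn. The section describes the tests as ones that patients are advised to have, not as tests that the study schedules. A patient with no new test still has a latest result, and that result enters the analysis as the 3-month outcome.

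At stake is the only laboratory outcome, which the Discussion relies on to back up the benefit of the intervention. A carried-over value weakens the comparison, and it also conceals that the outcome was never observed.

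**Working it through.** **1. The plan's own figure.** The only sample-size calculation is for diabetes distress: 44 per arm for a difference of 7.30 with 80% power. With a two-sided alpha of 0.05 and the cited control-arm SD at six months, 12.14 (the section does not say which SD it used):

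n per arm = 2 × (1.960 + 0.842)² × 12.14² / 7.30² = 2 × 7.849 × 147.38 / 53.29 = 43.4, rounded up to 44.

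The figure reproduces. It is not affected by this point, and no such calculation is given for HbA1c.

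**2. What the record rule lets through.** Take a patient enrolled at time 0, with sessions one week apart and the record read at 3 months.

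| Draw date of the latest result | Accepted by the record rule? | Consequence |
|---|---|---|
| Before enrolment (same result as baseline) | Yes | Change is exactly 0 |
| After enrolment, before the first session | Yes | Change owes nothing to the intervention |
| During the weekly sessions | Yes | Change reflects only part of the intervention |
| At the 3-month follow-up | Yes | Intended measurement |

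If the follow-up test is the rule, only the last row qualifies, and a patient who is not tested has a missing value. Under the record rule, the first three rows count as observed, so an analysis of missing data has nothing to act on.

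**3. Baseline.** Eligibility is defined at enrolment, but the value used is the latest one available at screening. Screening and enrolment follow each other closely, so those two moments need not conflict. What is open is how old the result may be when it is read.

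**4. Illustration of size.** Suppose a share f of 3-month values predates the sessions, equally in both arms and unrelated to how much a patient would benefit. Those patients contribute an expected between-arm difference of 0, so

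expected difference = (1 − f) × true difference.

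The effect on sample size depends on the analysis:

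- Comparison of 3-month values with the SD unchanged: factor 1/(1 − f)².
- Comparison of change scores, where the carried value is the baseline itself: the variance of the change also falls, to about (1 − f) of its value, so the factor is about (1 − f)/(1 − f)² = 1/(1 − f).

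For power, assume an HbA1c effect of the standardised size that 44 per arm detects with 80% power: (1.960 + 0.842) × √(2/44) = 0.597 SD. Power for 3-month values is then Φ[(1 − f) × 0.597 × √(n/2) − 1.960].

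| f (assumed) | Difference retained | Factor, 3-month values | Factor, change scores | Power, 44 per arm | Power, 60 per arm |
|---|---|---|---|---|---|
| 0% | 100% | 1.00 | 1.00 | 80.0% | 90.5% |
| 10% | 90% | 1.23 | 1.11 | 71.3% | 83.8% |
| 20% | 80% | 1.56 | 1.25 | 61.1% | 74.4% |
| 30% | 70% | 2.04 | 1.43 | 50.0% | 62.9% |
| 50% | 50% | 4.00 | 2.00 | 28.8% | 37.3% |

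Neither f nor an HbA1c effect size is in the document. Values drawn during the sessions would dilute less than this.

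**The case against.** The strongest reply is that the three places describe one procedure. Blood is drawn at the follow-up visit, the university laboratory runs it, the result is archived electronically under the patient's record number (Study setting), and the study reads it there. On that reading the latest result at 3 months is the follow-up test, and a carried-over baseline value arises only if the follow-up test is not done. This reading is possible, and using the record as a data source is no fault in itself. But no sentence ties the latest result to the follow-up test, and Measurement of HbA1c describes routine tests. Nor does the reading settle what happens when the follow-up test is missed, which is the case that matters.

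A second reply is that an article may leave time windows to the full protocol, and that Table 2, which holds the assessment schedule, is not shown. That stands against any complaint about a missing window alone. It does not remove the conflict between the rules that the article states.

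Third, HbA1c is absent from the Aim of the study section and is not the basis of the sample size. This limits the weight of the point, but HbA1c is still a named dependent variable.

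A reader might go further and infer that retesting would differ between the arms and so bias the comparison, or that the laboratory fee would keep patients from being tested. The text supports neither. Both arms have four weekly sessions and the same 3-month follow-up, and Study setting says that welfare funds meet treatment costs for patients who cannot pay (it does not name tests).

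**Conclusion.** The point holds as a conflict between stated rules for one outcome, with a defined consequence. As written, the record rule can supply a 3-month HbA1c drawn before or during the intervention, which gives a zero or diluted change and presents a missing outcome as an observed one. That follows from the wording and needs no assumption.

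The size cannot be established. The between-arm difference shrinks to (1 − f) of its true value if f is equal in both arms, and f is unknown. It would be wrong to read the table as a forecast for this trial, or to quote the larger sample-size factor as general: it applies only to 3-month values with an unchanged SD. The document also gives no ground for claiming that the bias favours either arm.

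The matter is worth correcting before analysis, but it does not touch the distress outcome or the sample size that rests on it.

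**What to change.** - In the Abstract and in Measurement of HbA1c, state that the 3-month HbA1c is the follow-up blood test described under Enrollment and data collection procedure, for every patient. It may be read from the record if that is convenient.
- Record the draw date of both the baseline and the 3-month value.
- State that a patient with no post-intervention draw at follow-up has a missing 3-month HbA1c. An earlier result is not carried forward, and the case goes into the planned sensitivity analysis for missing data.
- State how old a baseline record value may be, so that it fits the definition of suboptimal control at enrolment. The limit is for the investigators to choose.

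The cost is wording and the recording of two dates, since the follow-up test is already described in the article. The small downside is that some HbA1c values that would have looked complete will be counted as missing.

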#### Intervention and follow-ups

The intervention arm will receive 4 sessions based on DCM. These sessions will be conducted 1 week apart (45-60 min). These sessions will be facilitated by a trained educator. These sessions will include topics on managing diabetes, following a healthy lifestyle, starting insulin, and experiencing life with diabetes (Table 1).

**Table 1 Tab1:** Diabetic education using diabetes conversation maps

Session − 1	How Diabetes Works
DCM − 1	This is a standard 3 by 5 ft colorful drawing which is used to teach patients with diabetes, how it occurs, and how to manage potential complications.
Duration	45–60 min
Content	Drawings of situations familiar to people with diabetes. The facilitator will use these drawings to help the patients sitting in group to understand the disease.
Session-2	Living with Diabetes
DCM − 2	This is a standard 3 by 5 ft colorful drawings used to teach patients about daily self-care, hypo or hyperglycemia, and psychosocial adjustment
Duration	45–60 min
Content	Drawings of different situations familiar to the diabetic patients.
Session-3	Healthy Eating and Keeping Active
DCM − 3	This is a standard 3 by 5 ft colorful drawings used to teach patients about healthy eating habits and lifestyle habits
Duration	45–60 min
Content	Provides information about dietary choices and portion sizes, along with different types of physical activity.
Session-4	Starting Insulin or oral antidiabetic medication
DCM − 4	This is a standard 3 by 5 ft colorful drawings used to teach patients about the use of Insulin or other oral medications.
Duration	45–60 min
Content	Focuses on the natural progression of diabetes, as well as insulin therapy and its potential benefits for people with type 2 diabetes.

In control group, participants will attend routine diabetes counseling provided by diabetic clinics’ trained nurses. These counseling are routinely provided in groups and can range from 30 to 60 min at the time of outpatient visit to a diabetic clinic. For comparability between the intervention and control arms, we will arrange four routine counseling sessions (one week apart). Detail flow of the study including follow-ups and measurements at different time-points is shown in Table 2.

